### Follow-up

In both arms, follow-up will comprise standard of care, i.e., follow-up visit every 3 months with an MRI at 3 and 6 months and later if clinically relevant. Patients will be followed until one of the following events occurs: (i) death; (ii) end of study (max 64 months after start of inclusion) is reached; or (iii) patient withdraws informed consent. Quality of life questionnaires (EORTC QLQ-C30 + BN20 and EuroQol 5D-5 L) will be completed at baseline, < 72 h after surgical procedure, monthly for the first six months from randomization, subsequently at 12 and 18 months after randomization and thereafter yearly up to a maximum of 64 months [15–17]. Resource use and productivity losses will be measured monthly for the first six months from randomization, subsequently at 12 and 18 months after randomization and thereafter yearly up to a maximum of 64 months, using the iMTA Medical Consumption Questionnaire (iMCQ) and iMTA Productivity Cost Questionnaire (iPCQ) [18, 19]. Questionnaires will be filled in online through a secure web-based module, if necessary, with the help of a relative or caregiver. Adverse events will be monitored using the questionnaires and electronic patient files.

A detailed study flowchart is outlined in Fig. 1.

**Fig. 1 Fig1:**
[figure not shown]
Flowchart of study design

### Sample size

We hypothesize that LITT will improve the overall survival without substantially compromising the health-related quality-of-life. The two co-primary outcomes were used to calculate the required sample size.

#### Overall survival

Recent analysis of the Dutch Quality Registry Neurosurgery data showed a median survival of patients with primary irresectable glioblastoma in the Netherlands of 5.1 months [9]. Current available literature states that LITT in newly diagnosed, irresectable glioblastoma may improve the median survival to 10.2 months [12]. A doubling of current survival to 10.2 months (median survival benefit of 5.1 months) is considered relevant, based on input from experts, the Dutch Society for Neuro-Oncology, and the Dutch patient organization.

A Cox proportional hazards model (two-sided; alpha = 0.05; power = 90%) was used for sample size calculations. A hazard ratio of 0.5 was assumed for overall survival (equivalent to an improvement in median overall survival from 5.1 to 10.2 months). The null hypothesis assumed a hazard ratio of 1. The allocation ratio will be 1:1. With 46 months of accrual and 18 months of follow-up, after an average follow-up of 41 months we will have reached 96% of events (overall probability of event, pE = 0.96). The calculated sample size therefore is 91. To account for a 5% post-randomization exclusion rate due to non-glioma diagnosis on histopathology, a 5% drop-out ratio prior to intervention and 10% loss to follow-up, 114 patients (57 per arm) need to be included.

#### Final sample size

The total sample size will be 238 patients (119 per arm) as this will enable us to study both survival and quality of life.

### Loss to follow-up and exclusion

Patients who withdraw informed consent, who must be excluded after randomization or are lost to follow-up due to another reason will be included in the intention to treat analysis and will not be replaced.

### Data collection and management

All data will be collected in an electronic data capture system (CastorEDC). Data will be retrieved from electronic patient files and electronic questionnaires. Local investigators will be trained in data collection. Twice a year a monitoring visit will take place at each research location to check and guarantee the quality of the data.

### Statistical methods

#### Primary outcomes

Survival analysis will be performed on an intention-to-treat basis. Cox proportional hazard analysis (two-sided) will be performed at 0.05 significance level, adjusted for treatment center, to evaluate the difference in survival between groups. Survival curves for each group will be estimated with the Kaplan-Meier method. Median survival differences with 95% confidence intervals (CIs) will be derived from the Kaplan-Meier estimates.

In patients alive at 5 months post-randomization, differences in EORTC QLQ-C30 + BN20 scores between the two treatment arms will be calculated using linear regression, adjusted for treatment center, and will be reported as mean difference with one-sided 95%CI. Non-inferiority p-values will be calculated.

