## Introduction

Glioblastoma (GBM) is the most common and most malignant primary brain tumour [1]. These tumours account for around 60% of all primary brain tumours in adult patients with an incidence ranging from 3.9 to 4.17 per 100.000 persons [2]. GBMs are in most cases highly debilitating and often occur at a relatively young age (median 59 years) [3]. Although many efforts have been made to improve current therapies, patients with GBM face a poor prognosis, with a 5-year survival of 5% [4, 5]. Current standard of care includes surgical resection followed by adjuvant chemoradiation therapy (CRT) [6]. This strategy has been associated with median overall survival (OS) of 14.5–18.5 months, depending on the extent of resection [7, 8]. However, in 30% of patients surgery appears not to be feasible [9], most often due to the unfavourable location of the tumour, and sometimes because the patient does not desire surgical resection due to the possible complications and/or risk of further deterioration. These patients miss the benefit of surgical resection since biopsy followed by CRT results in a faster decline in quality of life and a median survival ranging from 5 to 9.4 months [10]. Laser-induced thermal therapy (LITT) (also referred to as Stereotactic Laser Ablation (SLA)), has been developed as a minimally invasive treatment for tumours, including brain tumours [11]. A recent systematic review, consisting of phase I and II studies, showed that the median survival in patients with newly diagnosed irresectable glioblastoma who received LITT is 10.2 months [12]. No data regarding the quality of life of patients who have undergone LITT is available. To date, no randomized controlled clinical trials looking at the effectiveness of LITT in patients with newly diagnosed irresectable glioblastoma have been published. A search on clinicaltrials.gov, ISRCTN Registry and EU clinical trials register for (ongoing) trials identified no (planned) randomized studies investigating the role of LITT in patients with newly diagnosed irresectable glioblastoma, precluding any conclusions on (cost-)effectiveness.

A preceding pilot study at Radboudumc [13] including 15 patients of which 10 treated with LITT showed that patients with an irresectable glioblastoma are willing to participate in a randomized trial. In addition, safety and feasibility data are acceptable and in line with previous reports [11, 14].

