### Randomization and study groups

Randomization will be performed by one of the study physicians using randomized permuted blocks of 4 and 6 through a web-based module (CastorEDC) which is available 7 days a week, 24 h per day. The randomization sequence is concealed and cannot be altered or predicted during the study. Assignments will be balanced in a 1:1 ratio between the two study arms, stratified by center. In the intervention arm, a maximum number of patients treated by each of the LITT centers will be set to 63 to avoid an uneven distribution of patients over the two LITT centers and to share the patient load.

Randomization will be done pre-operatively. It is not deemed feasible to randomize peri-operatively, since LITT requires specific hospital resources (staff, specific operation room and MRI time) which will need to be planned in advance and preferably within two weeks. The study will be open due to practicality and logistic reasons since patients from the intervention group need to be referred to one of the two LITT centers.

After inclusion, the patient will undergo biopsy or biopsy combined with same-session LITT within a maximum of 3 weeks.

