#### Secondary outcomes

Cox proportional hazard analysis (two-sided) will be performed to evaluate the difference in progression-free and disease-free survival between groups. Kaplan-Meier estimates will be used to assess progression-free and disease-free survival.

Additional Cox proportional hazard analysis will be performed on overall, disease-specific, and progression-free survival measured from time of treatment, KPS and tumor size. Tumor volume response will be calculated as mean differences with 95%CIs. Complications will be calculated as rate difference with 95%CIs. Generic HR-QoL effects will be calculated as mean differences between groups with 95%CIs. Longitudinal effects will be assessed using mixed model analysis. Effects on adjuvant treatment will be calculated as proportions not completing CRT and mean differences in duration of CRT course with 95%CIs.

To assess the cost-effectiveness, an economic evaluation will be performed from both a healthcare and a societal perspective, adopting a 1.5-year time horizon. Costs will be calculated according to the Dutch guideline for economic evaluation, by multiplying resource use with the corresponding unit costs. Average costs will be calculated in both groups and differences will be calculated inclusive of 95% confidence intervals. Effectiveness will be measured in terms of quality-adjusted life years (QALYs). QALYs will be based on the utility scores as measured with the EQ-5D-5 L, using the Dutch tariff and the area under the curve method. If relevant, incremental cost-effectiveness ratios (ICERs) will be calculated by dividing estimated differences in costs by differences in QALYs. Uncertainty will be addressed by means of non-parametric bootstrapping and where relevant one-way sensitivity analyses are performed.

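### The primary overall-survival Cox model adjusts for center only; adding baseline KPS, age and tumour size would gain power by an amount that depends on their unknown prognostic strength

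*Protocol article*

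**What the plan says.** Under Statistical methods, Primary outcomes, the article specifies for overall survival: "Cox proportional hazard analysis (two-sided) will be performed at 0.05 significance level, adjusted for treatment center". No other covariate is named, and the analysis is by intention to treat. Center is also the only stratification factor (Randomization and study groups): "Assignments will be balanced in a 1:1 ratio between the two study arms, stratified by center".

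KPS and tumour size are mentioned under Secondary outcomes: "Additional Cox proportional hazard analysis will be performed on overall, disease-specific, and progression-free survival measured from time of treatment, KPS and tumor size". The sentence places a time origin and two patient characteristics in one list, so it does not settle whether KPS and tumour size are covariates. Age is an eligibility criterion (Table 1) and enters no model.

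The sample size section states "A Cox proportional hazards model (two-sided; alpha = 0.05; power = 90%) was used for sample size calculations", and then "A hazard ratio of 0.5 was assumed for overall survival". It reaches 91 patients before losses and 114 after. The final 238 comes from the quality-of-life endpoint.

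**The concern.** Omitting prognostic covariates from a Cox model pulls the estimated treatment hazard ratio toward 1 and lowers power, even when randomisation is sound. With center as the only stratification factor and the only covariate, neither the design nor the primary analysis deals with chance imbalance in patient-level prognosis. KPS and age are already known from eligibility screening, so the information is available at no cost.

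The stake is the trial's main decision, because the Introduction requires superior survival (and non-inferior quality of life) before LITT is called effective. Power is ample at a hazard ratio of 0.5, but a weaker effect is possible on the article's own figures. The Introduction gives biopsy followed by chemoradiation "a median survival ranging from 5 to 9.4 months", and the design uses a control median of 5.1 months, near the bottom of that range. The midpoint, (5 + 9.4)/2 = 7.2 months, against 10.2 months would give a hazard ratio of 7.2/10.2 = 0.71 under exponential survival.

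**Working it through.** **1. Reproducing the plan's figure.** Inputs from the sample size section: two-sided alpha 0.05, power 90%, hazard ratio (HR) 0.5, 1:1 allocation, event probability 0.96, losses 5% + 5% + 10%.

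- Schoenfeld events: d = 4(1.960 + 1.282)² / (ln 0.5)² = 87.5.
- Patients: 87.5/0.96 = 91.1 (stated 91).
- After losses: 91/0.80 = 113.75, rounded up to 114 (stated 114).

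The plan's numbers reproduce.

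**2. Power at the final size, with no prognostic covariates.** Power = Φ(|ln HR|·√d/2 − 1.96).

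- Low case: 238 × 0.80 ≈ 190 evaluable, 190 × 0.96 = 182.4 events.
- High case: all 238 contribute, 238 × 0.96 = 228.5 events.

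| HR | 182 events | 228 events |
|---|---|---|
| 0.50 | 99.7% | 99.9% |
| 0.60 | 93.2% | 97.1% |
| 0.65 | 82.9% | 90.2% |
| 0.70 | 67.3% | 76.9% |
| 0.75 | 49.3% | 58.5% |

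The section on loss to follow-up and exclusion keeps all randomised patients in the intention-to-treat analysis, so the truth probably lies between the columns.

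**3. Gain from adjustment (simulation).** The setup was exponential survival with a control median of 5.1 months, censoring uniform between 18 and 64 months (46 months of accrual plus 18), and 1,500 to 3,000 runs per cell. Three independent standard normal covariates had an **assumed** total log-hazard SD. Center effects were not simulated. With three equal covariates, SD 0.3, 0.5 and 0.7 mean hazard ratios of exp(SD/√3) = 1.19, 1.33 and 1.50 per covariate SD.

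Power without → with the covariates, 190 patients, by conditional HR (gains taken before rounding):

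| HR | SD 0.3 | SD 0.5 | SD 0.7 |
|---|---|---|---|
| 0.50 | 99.1→99.6 (+0.5) | 97.7→99.3 (+1.6) | 93.9→99.5 (+5.6) |
| 0.55 | 95.9→97.4 (+1.5) | 91.6→97.4 (+5.8) | 85.8→97.4 (+11.6) |
| 0.60 | 88.5→92.0 (+3.5) | 82.3→91.8 (+9.5) | 71.3→90.9 (+19.7) |
| 0.65 | 76.8→82.7 (+5.9) | 68.3→79.9 (+11.5) | 60.2→81.7 (+21.5) |
| 0.70 | 60.7→66.3 (+5.5) | 51.5→64.8 (+13.3) | 42.9→64.2 (+21.3) |
| 0.75 | 41.9→47.1 (+5.2) | 39.9→49.5 (+9.7) | 31.1→48.9 (+17.7) |
| 0.80 | 28.5→31.9 (+3.3) | 23.8→31.3 (+7.5) | 20.3→29.2 (+8.9) |

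Simulation error is about a point per power figure (√(0.25/1500) = 1.3 points). In the HR 0.70, SD 0.5 cell, a 1,500-run estimate was +15.9; the 3,000-run value is shown.

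**4. Checks.** With SD 0 the two models differ by −1.1 to +0.2 points, so adjusting for uninformative covariates costs almost nothing. With all 238 patients and HR 0.60 to 0.70, the gains are 2 to 6 points (SD 0.3), 7 to 13 (SD 0.5) and 13 to 23 (SD 0.7). The attenuation is visible: at SD 0.5, a conditional HR of 0.65 appears as 0.69 in the unadjusted model.

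**The case against.** The case for leaving the model alone is substantial.

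- **The analysis is valid.** Adjusting for the stratification factor is conventional, type I error is preserved, and the significance level already allows for chance imbalance. This stands. A reader might infer bias or an error in the calculation; the article supports neither.
- **The declared effect is well covered.** The article takes 5.1 months from Dutch registry data, calls a doubling relevant, and randomises 238 where survival alone needs 114. This stands. An optimistic hazard ratio is a separate matter from covariate choice.
- **The size is not fixed.** A reader might infer that 10 or more points of power are lost whenever the effect is weaker than 0.5. That does not follow. With weak covariates the gain stays at or below about 6 points at every hazard ratio tried. At SD 0.5 it reaches 10 only around hazard ratios of 0.60 to 0.75. At a hazard ratio of 0.80 it is below 10 even with SD 0.7. Enrolling only KPS 70 or above also narrows the spread of KPS.
- **KPS and tumour size are already mentioned.** This stands in part. However, the additional analysis is described as "measured from time of treatment, KPS and tumor size", so on its face it starts at treatment and does not clearly provide an adjusted version of the intention-to-treat comparison.
- **Tumour size may not be available for everyone before randomisation.** This stands. Imaging exists at the tumour board stage, but the navigation MRI is made at admission, after randomisation, and 5% are expected to drop out before intervention.

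Mixed histology and patients who decline resection do not strengthen the case, because KPS, age and tumour size adjust for neither directly.

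**Conclusion.** The point holds as a modest, low-cost improvement. The primary survival model omits baseline covariates that the trial already collects or mentions, and every scenario with prognostic covariates favoured including them. At the planned hazard ratio of 0.5 little is at stake: 0.5 to 6 points, with power without the covariates at about 94% or more up to SD 0.7. For hazard ratios of 0.55 to 0.80 the gain is roughly 1.5 to 6, 6 to 13 or 9 to 21 points for weak, moderate or strong covariates with about 190 evaluable patients.

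These figures rest on an assumed prognostic strength, exponential survival and proportional hazards. They compare power on the same data, not estimates of the same hazard ratio. A statistical analysis plan may exist and was not seen, but the article itself commits to center as the sole covariate of the primary model.

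**What to change.** Before any comparative analysis, specify the primary overall-survival analysis as a Cox model from randomisation, in the intention-to-treat population, adjusted for center, baseline KPS and age. Add tumour size as measured on the diagnostic or pre-treatment MRI where available, and state which scan is used and how a missing value is handled. Report the center-only hazard ratio and the Kaplan-Meier medians alongside as supportive results. Reword the additional analysis so that the time origin and the roles of KPS and tumour size are separate.

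For KPS and age the cost is wording only, since both are recorded for eligibility. Tumour size may need a defined measurement on existing scans. The downside is that the adjusted hazard ratio is a conditional effect and will differ from the center-only one, so both must be shown, with the primary one named in advance.

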#### Secondary outcomes

Cox proportional hazard analysis (two-sided) will be performed to evaluate the difference in progression-free and disease-free survival between groups. Kaplan-Meier estimates will be used to assess progression-free and disease-free survival.

Additional Cox proportional hazard analysis will be performed on overall, disease-specific, and progression-free survival measured from time of treatment, KPS and tumor size. Tumor volume response will be calculated as mean differences with 95%CIs. Complications will be calculated as rate difference with 95%CIs. Generic HR-QoL effects will be calculated as mean differences between groups with 95%CIs. Longitudinal effects will be assessed using mixed model analysis. Effects on adjuvant treatment will be calculated as proportions not completing CRT and mean differences in duration of CRT course with 95%CIs.

To assess the cost-effectiveness, an economic evaluation will be performed from both a healthcare and a societal perspective, adopting a 1.5-year time horizon. Costs will be calculated according to the Dutch guideline for economic evaluation, by multiplying resource use with the corresponding unit costs. Average costs will be calculated in both groups and differences will be calculated inclusive of 95% confidence intervals. Effectiveness will be measured in terms of quality-adjusted life years (QALYs). QALYs will be based on the utility scores as measured with the EQ-5D-5 L, using the Dutch tariff and the area under the curve method. If relevant, incremental cost-effectiveness ratios (ICERs) will be calculated by dividing estimated differences in costs by differences in QALYs. Uncertainty will be addressed by means of non-parametric bootstrapping and where relevant one-way sensitivity analyses are performed.

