**Methods and analysis:**

The EMITT trial will be a multicenter pragmatic randomized controlled trial in the Netherlands. Seven Dutch hospitals will participate in this study. In total 238 patients will be randomized with 1:1 allocation to receive either biopsy combined with same-session MR-guided LITT therapy followed by CRT or the current standard of care being biopsy followed by CRT. The primary outcomes will be health-related quality of life (HR-QoL) (non-inferiority) using EORTC QLQ-C30 + BN20 scores at 5 months after randomization and overall survival (superiority). Secondary outcomes comprise cost-effectiveness (healthcare and societal perspective) and HR-QoL of life over an 18-month time horizon, progression free survival, tumour response, disease specific survival, longitudinal effects, effects on adjuvant treatment, ablation percentage and complication rates.

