The aim of this trial is to demonstrate whether same-session LITT is (cost-)effective in primary irresectable glioblastoma in the context of the program “Veelbelovende Zorg” of the Dutch Healthcare institute. This program aims to conditionally reimburse promising but expensive new treatments within a trial setting, to allow for the collection of high-quality evidence on its effectiveness and cost-effectiveness, which informs a definite reimbursement decision. When LITT proves to be effective, thus improving overall survival without compromising on quality of life, and appears to be cost-effective, the treatment will be included as a new standard treatment for this patient population and will be included in the Dutch basic healthcare reimbursement package.

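### The only stated economic horizon, 18 months, captures about half of the survival gain the trial assumes, so its ICER answers a narrower question than the reimbursement decision

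*Protocol article*

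**What the plan says.** The horizon is fixed in the statistical methods for secondary outcomes: "an economic evaluation will be performed from both a healthcare and a societal perspective, adopting a 1.5-year time horizon". The abstract agrees, listing cost-effectiveness and "HR-QoL of life over an 18-month time horizon" among the secondary outcomes. QALYs come from EQ-5D-5L utilities, "using the Dutch tariff and the area under the curve method". On uncertainty the article says only this: "Uncertainty will be addressed by means of non-parametric bootstrapping and where relevant one-way sensitivity analyses are performed". It gives no reason for stopping at 18 months and mentions neither a longer horizon nor extrapolation.

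The Follow-up section keeps patients in the study until death, withdrawal of consent or the end of the study, at most 64 months after inclusion starts. The EQ-5D-5L and the resource-use and productivity questionnaires (iMCQ, iPCQ) are collected monthly for six months, "subsequently at 12 and 18 months after randomization and thereafter yearly up to a maximum of 64 months".

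The Discussion describes a conditional reimbursement programme whose evidence on effectiveness and cost-effectiveness is collected in the trial, "which informs a definite reimbursement decision".

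**The concern.** LITT adds a procedure cost at the start and, if the trial's hypothesis is right, survival time that accrues over years. A horizon that ends while many LITT patients are still alive counts the whole procedure cost but only part of the QALYs gained. It also drops the later costs of care, so the net effect on the ICER is not obvious and has to be worked through.

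The stake is the reimbursement decision. According to the Discussion, LITT enters the basic package if it proves effective and cost-effective. If the only ICER stops at 18 months, the decision rests on a ratio that leaves out part of the benefit the trial was designed to detect, while data collected after month 18 have no stated economic use.

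**Working it through.** **Inputs from the article**
- Medians and hazard ratio (Sample size, Overall survival): "A hazard ratio of 0.5 was assumed for overall survival (equivalent to an improvement in median overall survival from 5.1 to 10.2 months").
- Survival model (Sample size, Quality-of-life): exponential, S(t) = 2^(−t/MST), where MST is median survival.
- Accrual 46 months plus 18 months of follow-up, 64 months in total; average follow-up 41 months; event probability 0.96.
- 119 patients per arm.

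**The plan's own figures first**
- Survival at 4.5 months: 2^(−4.5/5.1) = 0.542 and 2^(−4.5/10.2) = 0.737. The article states 54.2% and 73.6%.
- Survival sample size: "A Cox proportional hazards model (two-sided; alpha = 0.05; power = 90%) was used for sample size calculations". Events = (1.960 + 1.282)² / (0.25 × (ln 0.5)²) = 87.5; 87.5 / 0.96 = 91.1; stated 91.
- Mean event probability at 41 months under the exponential model: 0.967; stated 0.96.

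The plan's figures therefore agree with exponential survival at these medians.

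**Survival gain inside the horizon**

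Restricted mean survival to time T is (MST / ln 2) × (1 − 2^(−T/MST)).

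| Horizon | Control (months) | LITT (months) | Gain (months) | Share of lifetime gain |
|---|---|---|---|---|
| 18 months | 6.72 | 10.38 | 3.66 | 49.8% |
| 36 months | 7.30 | 13.44 | 6.14 | 83% |
| 64 months | 7.36 | 14.53 | 7.17 | 97% |
| Lifetime | 7.36 | 14.72 | 7.36 | 100% |

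Alive at 18 months: 8.7% of controls (about 10 of 119) and 29.4% of LITT patients (about 35 of 119).

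**Sensitivity to the survival model (an assumption range)**

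Weibull survival, S(t) = 2^(−(t/MST)^k), with both medians held:
- k = 0.8: 3.08 of 9.14 months, 34%.
- k = 1.2: 4.14 of 6.51 months, 64%.
- k = 1.5: 4.63 of 5.88 months, 79%.

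Holding the hazard ratio at 0.5 instead of the LITT median gives 30% at k = 0.8 and 87% at k = 1.5.

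**What this does to the ICER**

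The article gives no costs or utilities, so this is conditional. Let f be the fraction of the 18-month incremental cost that is the procedure. Let the rest scale with survival time, and let utility be constant. With 7.36 / 3.66 = 2.01, the 18-month ICER divided by the lifetime ICER is 2.01 / (f + 2.01 × (1 − f)):
- f = 1: 2.01
- f = 0.5: 1.34
- f = 0.25: 1.14
- f = 0: 1.00

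**How much later information the trial will have**

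This assumes uniform accrual, the exponential model and no loss to follow-up.
- Potential follow-up of at least T months is (64 − T)/46: 100% at 18 months, 61% at 36 months, 9% at 60 months.
- Survival time after month 18: LITT patients are expected to live 119 × 14.72 × 0.294 = 515 patient-months, of which 358 (69%) fall inside planned follow-up. For controls it is 64 of 76 (84%).
- Alive and under observation at 30 months, the first yearly form if counted from month 18: controls 119 × 0.017 × 34/46 = about 1.5; LITT 119 × 0.130 × 34/46 = about 11. If that form is due at 24 months instead, about 4 and 20.

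**The case against.** The strongest defence is that 18 months is the last point to which every patient can be followed. The 64 months are counted from the start of inclusion, so only the earliest patients can come near that limit. A reader might infer that the trial observes its patients for 64 months and simply discards the data; the Follow-up section does not support that. This part of the defence stands, and it makes 18 months a reasonable base case.

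Late utilities and costs will also be sparse. With about 1.5 controls and 11 LITT patients at 30 months, before any loss to follow-up, post-18-month values for controls would be close to pure extrapolation. The Discussion itself expects questionnaire completion to fall over time. This stands too. Survival time is better served than the questionnaires, since most of it after month 18 falls inside planned follow-up.

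A reader might further infer that the planned ICER is biased against LITT whenever the survival hypothesis is true, or that it is twice too high. Neither can be shown. An 18-month ICER estimates an 18-month ICER correctly. Later costs are cut off along with later QALYs, and the doubling is the limiting case in which the procedure is all of the incremental cost. If late care is costlier or late utility lower, the effect shrinks and could reverse.

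Finally, a condensed article may leave extrapolation methods and discount rates to a fuller document, and its one-way sensitivity analyses are not listed. That is fair for the details. The horizon itself, however, is a stated choice, and it is that choice that is at issue.

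**Conclusion.** The point holds as a weakness in a stated analysis choice. It is not a contradiction, because the abstract and the methods agree on 18 months, and it is not a calculation error.

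Under the plan's own survival assumptions, the stated horizon captures about half of the expected life-months gained, and between about a third and four fifths across the Weibull range with the same medians. These are shares of life-months. The share of QALYs depends on utilities after month 18, which the article does not give.

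Because the procedure cost falls inside the horizon and part of the survival gain falls outside it, the 18-month ICER probably overstates the longer-run ICER. The size is unknown: under the exponential model with constant utility, it runs from nil to about two-fold according to how much of the incremental cost is the procedure.

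Cost-effectiveness is a secondary outcome, and neither co-primary analysis is affected. The point matters because the economic result feeds a reimbursement decision.

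**What to change.** Keep 18 months as the base within-trial analysis. Pre-specify a second, co-reported scenario that:
- uses all available follow-up for survival and the EQ-5D-5L, iMCQ and iPCQ data already collected after month 18;
- adjusts costs and QALYs for censoring at the end of the study;
- extrapolates survival under several distributions, and reports the spread;
- applies discounting;
- states the assumptions made for late utilities and costs, and how many patients per arm inform them.

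Report both ICERs to the reimbursement body and label the second as partly extrapolated.

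The cost is extra health-economic modelling; no new data collection is needed. The downside is that utilities and costs after month 18, above all in controls, rest on very few patients, so the scenario will depend heavily on its assumptions.
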